## Abstract

**Background:**

Gastroschisis is a congenital abdominal wall defect characterized by severe gut dysmotility. These neonates often face lengthy hospital stays, prolonged parenteral nutrition dependence, and complications such as growth faltering, sepsis, and intestinal failure. Feeding practices for neonates with gastroschisis vary and emphasize extended bowel rest and delayed feeding initiation. Usual practices in determining timing to start feeds include awaiting return of bowel function which typically consists of low Replogle output volume, color changing from bilious to clear and/or passing stool. However, emerging studies suggest that early initiation of feeds through standardized protocols may improve outcomes. The Gastroschisis And Early Infant Nutrition (GAIN) Study aims to test the feasibility of an early feeding approach in neonates with simple gastroschisis.

**Methods:**

This two-site single-arm feasibility trial aims to enroll neonates with presumed simple gastroschisis over 30 months. The intervention has two main components: Replogle suction tube removal within 24 h of abdominal closure and starting small-volume human milk feeds within 48 h of abdominal closure. Feeding volume will be advanced as tolerated, following the University of California Fetal Consortium pathway, which is standard care. Feasibility outcomes include enrollment rate, protocol adherence, fidelity, and withdrawal rate. Exploratory outcomes include hospitalization length, time to full feeds, duration of parenteral nutrition, use of human milk, breastfeeding rates, and anthropometric measurements. Safety measures involve monitoring for feeding-related complications, infections, and unexpected surgical interventions.

**Discussion:**

This feasibility trial of early feeding initiation in neonates with gastroschisis is a critical step towards addressing the need for a standardized feeding approach. Findings will inform future clinical trials and challenge the need for prolonged bowel rest. Standardizing early feeding practices could reduce practice variation, improve gut motility, and the overall health of neonates with gastroschisis.

**Systematic review registration:**

NCT06878950

## Introduction

### Gastroschisis: clinical significance

Gastroschisis is a complex and costly birth defect characterized by the protrusion of fetal intestines through a hole in the abdominal wall. Neonates with gastroschisis carry significant morbidity, including prolonged hospitalization and parenteral nutrition (PN), high rates of growth faltering (30–55%), sepsis (19%), cholestasis (14–26%), and short bowel syndrome (7%) [1–4]. The mean cost for hospitalization for neonates with gastroschisis in the USA was $85,080 USD in 2019. Thirty-eight percent of these neonates were readmitted within the first year of age at an average cost of $186,873 USD [5]. Recent data suggest a decline in the prevalence of gastroschisis following decades of a steady increase. However, gastroschisis continues to affect 1.60 to 2.46 per 10,000 live births in the U.S. and primarily affects young mothers [6]. Despite this recent epidemiological shift, gastroschisis is the leading cause of pediatric intestinal failure, a multi-factorial disorder that carries substantial long-term consequences including malnutrition, stunted growth, central catheter-related infections and emboli, intestinal-failure-associated liver disease, neurodevelopmental impairment and psychosocial problems [1, 3, 7–9].

### Management challenges and variability in practice: need for standardization

Despite surgical repair, these neonates often have intestinal dysmotility, resulting in feeding intolerance, prolonged PN courses, and extended hospital stays. On average, neonates with gastroschisis receive their first feed at 15 days of life and require 25 PN days [1, 4, 10]. Management of neonates with gastroschisis varies widely across and within health systems. Clinicians lack evidence-based guidelines, particularly regarding feeding practices [11]. Usual practices in determining timing to start feeds include awaiting return of bowel function which typically consists of a combination of decreasing Replogle output volume, color changing from bilious to clear and/or passing stool. This variability in feeding may contribute to delays in achieving full enteral nutrition and prolong PN exposure and hospitalization.

The University of California Fetal Consortium (UCfC) implemented a standardized pathway (Fig. 1) across eight medical centers. Key advancements include consistent adherence to standardized protocols across institutions, resulting in statistically and clinically significant decreased ventilator days, decreased antibiotic days, and earlier initiation of enteral feeds [12]. While a standardized approach to nutrition improved growth, the duration of PN and length of stay (LOS) remained unchanged [4]. These results reflect unresolved barriers in transitioning to full enteral autonomy.

**Fig. 1 Fig1:**
[figure not shown]
The UC Fetal Consortium (UCfC) Gastroschisis Clinical Pathway. Guidelines for managing neonates with gastroschisis currently used at sites across the UCfC. Created in BioRender. https://BioRender.com/mdt9g3m

### Benefits of early enteral feeding practices

Growing evidence indicates that early introduction of enteral feeds in neonates with simple gastroschisis improves clinical outcomes [13–16, 18]. Traditionally, prolonged bowel rest was favored after surgical closure of the defect; however, mounting evidence suggests this practice may be unnecessary and potentially counterproductive to normal bowel functional maturation [13–16]. Meta-regression analyses in neonates with gastroschisis have demonstrated that each day delay in starting enteral feeds is associated with 1.4 additional days to reach full enteral feeds, 2.1 additional PN days, and 1.9 additional hospital days [17]. Early feeding, in neonates with and without gastroschisis, is also associated with improved weight gain and reduced intestinal inflammation, which may lead to a decrease in morbidity [13, 18, 19].

Despite accumulating evidence favoring early enteral feeding in gastroschisis, critical knowledge gaps hinder consensus guidelines [4, 11, 18, 20]. The absence of randomized controlled trials evaluating feeding protocols limits definitive recommendations, and institutional variability in existing protocols complicates comparative effectiveness analyses.

### Rationale for the Gastroschisis And Early Infant Nutrition Study (The GAIN Study)

The GAIN Study addresses a significant gap in the management of neonates with gastroschisis. Demonstrating the feasibility of a standardized approach to early feeding is a critical initial step towards helping to reduce unnecessary practice variation, shorten PN dependency and hospitalization, and improve both short and long-term outcomes for these vulnerable neonates and their families [18]. This protocol is based on a modified version of the gastroschisis feeding protocol implemented in Australia by Hobson et al*.* [18, 21]. This protocol was adapted in order to incorporate differences in current practices within the institutes of the UCfC. Ultimately, this study could have a significant impact on feeding practices for neonates with gastroschisis across the US and possibly worldwide.

## Objectives

We will test the feasibility of conducting a trial of initiating early introductory, gut-priming enteral feeds (1 mL every 4 h) within the first 48 h after abdominal closure in neonates with gastroschisis in a level III/IV neonatal intensive care unit (NICU). Feasibility will assess enrollment, protocol adherence, fidelity, withdrawal rate, and safety.

## Trial design

This study is a single-arm feasibility trial. All enrolled neonates will receive the intervention. This trial is not designed to test hypotheses regarding efficacy.

## Methods: participants, interventions and outcomes

### Study setting

This multi-site study will take place in two academic hospitals: University of California Davis and University of California Los Angeles. University of California Davis is a 121-bed children’s hospital within a large academic medical center in Northern California; the NICU has 49 beds and accepts patients from over 33 counties from a 65,000-mile region that includes Northern California, Southern Oregon, and Nevada. University of California, Los Angeles is a 90-bed children's hospital with a large academic medical center in Southern California; the NICU has 22 beds and accepts patients from over 18 cities or communities within and beyond Los Angeles County.

### Eligibility criteria

Eligible neonates will have presumed simple gastroschisis born at ≥ 34 weeks of gestation who are hemodynamically stable (not on pressors for blood-pressure support), born to mothers ≥ 16 years old and speak English or Spanish. Simple gastroschisis is defined as gastroschisis without associated intestinal complications—specifically, in the absence of atresia, necrosis, perforation, or volvulus. Deciding whether a neonate has presumed simple gastroschisis is a decision the GAIN study team, comprising of neonatologists and pediatric surgeons, will make in consultation with the primary medical and surgical teams. The pediatric surgeons will inspect the bowel, and the GAIN study team will gather this information and discuss any findings with the primary teams and make a preliminary determination of whether the infant qualifies. Exclusion criteria include complex gastroschisis at time of closure or solidified by definitive operative findings (any ischemic bowel, intestinal perforation, or obvious atresia with mesenteric defect), major congenital anomalies, ionotropic medications, neonates who are wards of the state, futile or redirection of care, participation in another interventional trial, and anyone deemed unfit for participation by study investigators or the primary medical team. A major congenital anomaly is a structural or functional defect present at birth that will have significant impact on the individual, including surgical, medical or serious cosmetic significance [22].

### Who will take informed consent

Trained study personnel will obtain informed consent antenatally when feasible or postnatally, prior to intervention initiation. Participation is voluntary and will not affect clinical care. The feeding protocol is implemented by the clinical team for enrolled participants; parents are not responsible for administering the intervention.

### Interventions

#### Explanation for the choice of comparators

This study is a single-arm feasibility trial, whereby every enrolled neonate is assigned to the intervention. Thus, a comparator group is not included. Because gastroschisis is rare, this single-arm design will optimize our ability to assess enrollment, protocol adherence, fidelity, withdrawal, and safety.

#### Intervention description

The intervention includes implementing a Gastroschisis Early Feeding Protocol (Fig. 2). Specifically, for study patients, clinical practice is changed by removal of the Replogle suction tube within 24 h of abdominal closure and the initiation of introductory, gut-priming feeds (1 ml every 4 h) within 48 h of abdominal closure. The primary medical team can advance to trophic feeds (10–20 ml/kg/day) based on clinical tolerance, and then resume the standard care pathway, which advances feeds by approximately 20 ml/kg/day as tolerated. If the parents decline to consent, neonates will follow our current standard UCfC Gastroschisis Pathway (Fig. 1). Direct breastfeeding is allowed for both study patients and non-study patients if the neonate is tolerating enteral feeding of 80 ml/kg/day for at least 2 days. Our study defines feeding tolerance as an infant who is well appearing, and has a reassuring abdominal exam, nonbloody stools, and stable vital signs. Infants may have small frequent nonbilious, nonbloody spit ups. If the infant is not tolerating feeds, Pediatric Surgery should be notified and feedings should be suspended. A Replogle may be placed and/or imaging may be required (Fig. 2).

**Fig. 2 Fig2:**
[figure not shown]
GAIN Study Feeding Protocol. Building on the UCfC Gastroschisis Nutrition Pathway, the primary change involves removing the Replogle within 24 h of abdominal closure and initiating introductory feeds to simulate peristalsis and continued maturation of the intestine. Created in BioRender. https://BioRender.com/eavktjs

#### Criteria for discontinuing or modifying allocated interventions

The intervention may be discontinued or modified for the following reasons: parent request, classification as complex gastroschisis (finding of intestinal perforation, atresia, necrosis), feeding intolerance, ill appearing, need for mechanical ventilation, vasoactive medications, or clinician judgment.

#### Strategies to improve adherence to interventions

Strategies to improve adherence include educational sessions for clinical staff, feedback from medical teams, appointment of champions, pre-delivery huddles, visual paper reminders at bedside and weekly check-ins. Adherence will be monitored using protocol checkpoints highlighted in study materials, such as confirming Replogle tube removal within 24 h and initiating enteral feeds within 48 h of abdominal closure.

#### Relevant concomitant care permitted or prohibited during the trial

No concomitant medications or interventions are prohibited. All concomitant care will be documented throughout the study.

#### Provisions for post-trial care

Provisions for ancillary and post-trial care are not planned as part of this study.

### Outcomes

#### Feasibility objective outcomes

We will test the feasibility of implementing an early feeding protocol for neonates with gastroschisis. Feasibility will be assessed through:Objective 1 Enrollment (primary feasibility objective): obtain consent from ≥ 80% of eligible neonates’ parents/guardians from the prenatal period to within the first 24 h of abdominal closure.Objective 2 Protocol adherence: ≥ 85% of enrolled neonates receive introductory feeds within 48 h of abdominal closure.Objective 3 Fidelity: feeding protocol adherence with ≥ 90% of predefined protocol steps.Objective 4 Withdrawal: < 10% of enrolled neonates withdraw.

#### Exploratory outcomes

Data will be collected prospectively via electronic health records. These measures will be compared to a historical cohort using the existing UCFC database, which has been previously approved by IRB protocol # 2216195–2 at UC Davis, and IRB protocol # 24–6179 at UCLA.

Exploratory clinical endpoints will include (1) length of hospitalization (days), (2) time to initiation of feeds from final abdominal closure (days), (3) time to full feeds (100 mL/kg/day or PO ad libitum whichever comes first) from final abdominal closure (hours), (4) duration of parenteral nutrition (days), (5) days of any human milk which includes parent’s own milk and/or donor breast milk during hospitalization, (6) any direct breastfeeding during hospitalization, (7) any direct breastfeeding at discharge (defined as 48 h prior to hospital discharge) (8) any use of parent’s own milk at discharge (defined as 48 h prior to hospital discharge), (9) growth parameters (delta-z-scores for weight and length (discharge–admission measurements).

The length of hospitalization refers to the total number of days spent in the hospital during the initial birth hospitalization. Generally, this will be days in the neonatal intensive care unit (NICU) but can also be days in the pediatric intensive care unit (PICU) or pediatric wards. This will be measured via midnight census data from electronic health records (EHR). Feeding progression covers the initiation of feeds, defined as time to first feed and time to full feeds, both in days. The duration of PN is measured as the number of days of PN. Rates of direct breastfeeding are defined as direct breastfeeding 48 h before discharge. Outcomes of adverse events include rates of necrotizing enterocolitis (> Stage II), sepsis, abdominal compartment syndrome, additional abdominal surgeries (excluding primary closure), and mortality. Medical errors and adverse events will be obtained via solicited reports and review of EHR data.

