#### Methods for additional analyses, including comparisons to historical controls

We recognize that accounting for specific confounders, such as site, gestational age, birth weight, sex, and race/ethnicity, is important. If feasible, we may consider performing sub-analyses or accounting for these variables in specific models. However, we recognize that our sample size is small and our results most likely will not be generalizable.

For comparisons to historical controls on the study variables described earlier, we anticipate being able to obtain patient-level data from the historical controls, permitting us to use linear and logistic regression to estimate adjusted mean differences or adjusted odds ratios, respectively, with 95% confidence intervals for the current vs. historical control comparisons, adjusting for study site. Continuous outcomes may be log-transformed to improve the validity of the normality assumption, with the Van Elteren test (stratified Wilcoxon Mann–Whitney) used as a backup if parametric tests are not appropriate. If patient-level data from the historical controls is not available but means and/or proportions are available, we will instead estimate stratified means and/or proportions for the current cohort with 95% confidence intervals, permitting comparisons to the historical means and proportions.

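### The historical comparison of growth models change in z-score with adjustment for site only; adding the admission z-score, and reporting both estimates, would be a better default, above all for length

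*Protocol article*

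**What the plan says.** In the protocol article, Exploratory outcomes, the ninth endpoint is "growth parameters (delta-z-scores for weight and length", taken as discharge minus admission. Of all the exploratory measures the section says: "These measures will be compared to a historical cohort using the existing UCFC database".

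Methods for additional analyses, including comparisons to historical controls, gives the model. If patient-level control data are obtained, continuous outcomes go into a linear regression, with intervals "for the current vs. historical control comparisons, adjusting for study site". Site is the only covariate committed to.

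The same section recognises that "accounting for specific confounders, such as site, gestational age, birth weight, sex, and race/ethnicity, is important", but leaves that adjustment open: "If feasible, we may consider performing sub-analyses or accounting for these variables in specific models". The list contains neither an admission z-score nor any measure of length.

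Two other routes are named. A site-stratified rank test is the backup if the parametric model is unsuitable. If only historical summaries are available, "we will instead estimate stratified means and/or proportions for the current cohort with 95% confidence intervals".

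**The concern.** A regression of change in z on cohort and site is a regression of discharge z on the same terms with the coefficient of admission z set to 1. Where the true coefficient is smaller, infants who start low tend to gain z and infants who start high tend to lose it, however they are fed.

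The cohorts are not randomised. Trial infants are selected on gestation, haemodynamic stability, presumed simple disease and parental consent, and the article does not say that the historical cohort is restricted in the same way. With about 20 trial infants, chance imbalance adds to this. A difference in mean admission z is therefore plausible, although its size and direction are unknown.

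Part of any such difference could be read as a growth effect of early feeding. If trial infants enter with higher z-scores, the feeding protocol looks worse than it is; if they enter lower, it looks better. The interval is also wider than the same data allow. The article expects its findings to inform later trials, so a growth difference with an interval may be taken as a signal.

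**Working it through.** **The plan's own figures.** The article gives no precision figure for growth. Its only precision figures are for the feasibility proportions (Sample size), and they reproduce: 1.96 × √(0.25/40) = 15.5 points and 1.96 × √(0.25/20) = 21.9 points, against the stated limits of 16 and 22.

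**Inputs.** From the article: the endpoint is discharge z minus admission z, the model contains cohort and site, 20 infants are to be enrolled, and intervals are at 95%. Assumed, because the documents give none of them: SD of z = 1 at both times, correlation ρ = 0.5 to 0.8, difference D in mean admission z (current minus historical) = 0.1 to 0.5, and 100 historical infants. With equal SDs the slope equals ρ.

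**Bias.** Suppose both cohorts follow one line: discharge z = a + slope × admission z + effect of cohort. Subtract admission z and take the difference between cohorts:

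difference in mean change = effect + (slope − 1) × D

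| Slope | D = 0.1 | D = 0.3 | D = 0.5 |
|---|---|---|---|
| 0.5 | −0.05 | −0.15 | −0.25 |
| 0.7 | −0.03 | −0.09 | −0.15 |
| 0.8 | −0.02 | −0.06 | −0.10 |

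**Precision.** The variance of the change is 2s²(1 − ρ). The residual variance with the baseline in the model is s²(1 − ρ²). Their ratio is (1 + ρ)/2, and the ratio of standard errors is its square root. For 20 against 100 infants, the 95% half-width is 1.96 × √(variance) × √(1/20 + 1/100), where √0.06 = 0.245.

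| ρ | Variance ratio | SE ratio | Half-width, change with site only | Half-width, with baseline |
|---|---|---|---|---|
| 0.5 | 0.75 | 0.866 | 0.48 | 0.42 |
| 0.7 | 0.85 | 0.922 | 0.37 | 0.34 |
| 0.8 | 0.90 | 0.949 | 0.30 | 0.29 |

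Adding the baseline thus cuts the standard error by about 13%, 8% and 5%. These ratios are slightly optimistic when the cohorts differ at baseline. In the first simulation below, the empirical standard errors were 0.190 and 0.177, a ratio of 0.93 rather than 0.92.

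**Simulation checks** (20 against 100 infants, ρ = 0.7, D = 0.3, no true cohort effect):

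1. Common regression line: the site-only change score is off by −0.090 and the baseline-adjusted model by 0.000.
2. Equal true mean change in both cohorts despite D: the site-only change score is off by 0.003 and the baseline-adjusted model by 0.093.
3. Common regression line, with birth weight, gestational age and sex added to site: the error for weight falls from −0.085 to 0.002. Here birth weight was generated from the admission weight z-score, gestational age and sex, so this shows what those three can do when admission weight is close to birth weight.

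Simulation error is about 0.19/√4000 = 0.003 for checks 1 and 2, and 0.19/√2000 = 0.004 for check 3.

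**The case against.** **Baseline adjustment is not a guaranteed correction.** A reader might infer that any baseline difference must distort the site-only result and that adding the admission z-score removes the distortion. The documents do not support that. Without randomisation this is Lord's paradox: the change score and the adjusted model are each unbiased under a different assumption, and the data cannot decide between them. Check 2 shows the adjusted model off by as much as the change score is in check 1. This objection stands. It is a reason to report both estimates, not a reason to rely on the change score alone.

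**Weight is largely anticipated.** The optional birth weight, gestational age and sex together come close to determining admission weight z, and in check 3 they removed almost all of the bias. A reader might take weight and length to be equally exposed; they are not. For weight the gap is a missing commitment. For length, no listed covariate does the same job.

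**The sizes are assumed and modest.** This stands. No SD, correlation, baseline difference or historical number is given, and nothing in the article shows that the cohorts do differ at admission. At D = 0.3 the bias is 0.06 against a half-width of 0.30 (ρ = 0.8), or 0.15 against 0.48 (ρ = 0.5): about a fifth to a third of the half-width.

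**This is detail for an analysis plan, on an exploratory endpoint.** The exploratory status is real and sets the priority: the article states that the trial tests no efficacy hypothesis, and it already warns that the sample is small. But the article is not silent here. It states an adjustment set, and that set omits a value without which the endpoint cannot be computed. An analysis plan that is not shown may add it, and nothing in the article forbids it.

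**Conclusion.** The point holds as a low-priority improvement. The only model committed to for change in z adjusts for site alone and so fixes the slope on admission z at 1. If the slope is below 1 and the cohorts share a regression line, the comparison is biased by (slope − 1) × D, or −0.06 to −0.15 z for an assumed D of 0.3 and slopes of 0.8 to 0.5. With equal SDs, leaving out the baseline forgoes a cut in standard error of about 5% to 13% for correlations of 0.8 to 0.5. Length is the clearer gap, since not even an optional covariate covers it.

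The point does not show that the planned growth result will be wrong. It affects no feasibility objective.

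**What to change.** In Methods for additional analyses, including comparisons to historical controls, add for endpoint 9:

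*Where patient-level historical data are available, the model for change in weight (length) z-score includes the admission weight (length) z-score as well as study site. The estimate adjusted for site only is reported alongside. Without randomisation the two estimates rest on different assumptions that cannot be tested, and a disagreement between them will be read as uncertainty about the growth difference.*

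Change in z can stay as the reported outcome: once the admission z-score is in the model, the cohort coefficient is the same as with discharge z as the outcome.

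The cost is one covariate and one extra estimate per growth model. No new data are needed, because any patient-level change in z already requires the admission value; if the historical database lacks admission length, the length comparison itself cannot be made. The fix does not apply to the summary-data fallback, and the site-stratified rank test has no place for the covariate. Settling this before the historical comparison is run also prevents a choice between the two models after the results are seen.

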### Data collection and management

#### Plans for assessment and collection of outcomes

Feasibility objectives will be assessed by tracking the number of neonates approached, enrollment rates, milestone achievement (such as initiation of feeds within 48 h of abdominal closure), and withdrawal rates. Data for the intervention group will be collected prospectively from the electronic health record (EHR) prenatally and through the initial hospital discharge.

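### Length of stay and PN days include time before abdominal closure, so a cohort difference in time to closure would pass into the historical comparison

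*Protocol article*

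**What the plan says.** The Protocol article, Exploratory outcomes, lists nine clinical endpoints. Four of them measure time, and they do not share an origin.

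- Endpoint 1: "The length of hospitalization refers to the total number of days spent in the hospital during the initial birth hospitalization".
- Endpoint 2: "time to initiation of feeds from final abdominal closure (days").
- Endpoint 3, time to full feeds, is defined as "whichever comes first) from final abdominal closure (hours").
- Endpoint 4: "The duration of PN is measured as the number of days of PN".

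Data for enrolled infants "will be collected prospectively from the electronic health record (EHR) prenatally and through the initial hospital discharge" (Plans for assessment and collection of outcomes), so pre-closure days lie inside the data window.

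The intervention is timed from closure: "removal of the Replogle suction tube within 24 h of abdominal closure and the initiation of introductory, gut-priming feeds" (Intervention description).

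On the comparator, the protocol states: "These measures will be compared to a historical cohort using the existing UCFC database". The section on additional analyses and historical controls plans linear or logistic regression with 95% confidence intervals, adjusted for study site. It names gestational age, birth weight, sex and race/ethnicity as further confounders that may be considered if feasible. Neither time to closure nor type of closure is among them.

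**The concern.** Days before closure cannot respond to an intervention that starts at closure. Consent may be given up to 24 h after closure (Feasibility objective outcomes), so some of those days can even precede enrolment. They still count in endpoint 1, and in endpoint 4 whenever PN was running. The word final in endpoints 2 and 3 suggests that closure is not always a single event at birth.

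Take two infants with the same course after closure, one closed on day 0 and one on day 7. They differ by 0 days on endpoints 2 and 3, by 7 days on endpoint 1, and by up to 7 days on endpoint 4. If the mix of such infants differs between the current and historical cohorts, the contrast moves although feeding did nothing.

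The Introduction gives shorter PN and shorter hospitalization as reasons for the study, and the abstract says the findings will inform later trials. A planner of the next trial would therefore look at these two contrasts.

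**Working it through.** **1. The plan's own figure.** The protocol gives no precision or effect figure for length of stay or PN days. Its only computed design figure is the margin for the feasibility proportions (Sample size). It reproduces: 1.96 × √(0.25/40) = 15.5 points, stated as below 16, and 1.96 × √(0.25/20) = 21.9 points, stated as below 22. It does not bear on this point.

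**2. Identity for length of stay.** Let C be days from birth to final closure and P days from closure to discharge.

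- Length of stay = C + P, so the cohort difference is ΔC + ΔP.
- With no feeding effect and no other difference after closure, ΔP = 0 and the contrast equals ΔC.
- Adjustment for site does not remove a ΔC that is present within sites.

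**3. Identity for PN days.** Let f be the share of pre-closure days on PN, taken as equal in both cohorts. The PN contrast is then f × ΔC with 0 ≤ f ≤ 1, so up to one for one. The protocol does not give f.

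**4. Scale.** The section on benefits of early enteral feeding cites 1.9 hospital days and 2.1 PN days per day of delay in starting feeds. ΔC is not given anywhere. The range of 1 to 5 days is an assumption.

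| Assumed ΔC (days) | Shift in stay | Shift in PN days | Same as a change in feed start of: stay, ΔC/1.9 | PN with f = 1, ΔC/2.1 |
|---|---|---|---|---|
| 1 | 1 | 0 to 1 | 0.53 | 0.48 |
| 2 | 2 | 0 to 2 | 1.05 | 0.95 |
| 3 | 3 | 0 to 3 | 1.58 | 1.43 |
| 5 | 5 | 0 to 5 | 2.63 | 2.38 |

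The last two columns only rescale the assumption. They are not evidence that a shift exists.

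**5. Simulation with zero feeding effect.** Assumed: 20 current and 100 historical infants, two sites, C gamma with shape 2 and scale 2 (mean 4 days), P gamma with shape 4 and scale 7 (mean 28 days), C and P independent, least squares adjusted for site, 1,000 runs per row. Historical infants close later by ΔC.

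| ΔC | Mean difference, total stay | Mean difference, closure to discharge | 95% CIs for total stay excluding 0 |
|---|---|---|---|
| 0 | -0.05 | -0.08 | 5.2% |
| 1 | -1.14 | -0.12 | 5.4% |
| 2 | -1.96 | 0.08 | 8.2% |
| 3 | -2.94 | 0.04 | 14.3% |
| 5 | -4.86 | 0.13 | 28.7% |

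The identity is confirmed. Noise is large beside it: the assumed variances are 2 × 2² = 8 and 4 × 7² = 196, so the standard error is about √204 × √(1/20 + 1/100) = 3.5 days and the half-width about 1.96 × 3.5 = 6.9 days.

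**6. What the simulation cannot show.** It draws C and P independently, so the closure-anchored count is unbiased by construction. Suppose instead that each day of later closure shortens the post-closure course by k days, with 0 ≤ k ≤ 1. Then P = R - kC, where R does not depend on C. With no feeding effect the total shifts by (1 - k)ΔC and the closure-anchored count by -kΔC. At k = 0 only the total is distorted, and at k = 1 only the anchored count. In between, the two err in opposite directions.

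**The case against.** The strongest reply is that this is a choice of what to measure, not an error. Total hospital days and total PN days are the burden on the family and the health system, and the Introduction states its own PN benchmark as a total of 25 days. That stands. A reader might infer that the totals are wrong and should be replaced, but the documents do not support this. By step 6, a closure-anchored count alone is clean only if recovery starts at closure.

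Second, nothing shows that the bias exists. No closure times are given for either cohort, and no shift in staged closure is reported. The comparator is a consortium database approved at the same two sites, and the consortium uses a standardized pathway. That stands too. A reader might infer that the length-of-stay and PN comparisons are biased. The documents support only that they are unprotected.

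Third, a one-for-one shift is too strong for PN days, because the text does not say that PN runs through the whole period before closure. Correct, hence the wording up to one for one.

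Fourth, the list of confounders is open-ended, and an analysis plan that is not shown may add closure timing. That is possible, but the protocol fixes the endpoint definitions themselves and commits only to site.

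Fifth, Trial design disclaims efficacy testing, and the additional-analyses section concedes the small sample. This limits the weight of the point. It does not remove it, because adjusted differences with confidence intervals are still planned.

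A reader might also infer a marked loss of precision from the pre-closure days. Under the assumed distributions they raise the variance only from 196 to 204, about 4%.

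**Conclusion.** The point holds, and it is minor. Endpoint 1 explicitly includes days before closure. Endpoint 4 includes them by its unanchored definition and the data window, although the text does not say from birth. Endpoints 2 and 3 and the intervention itself start at closure. Since the committed adjustment is for site only, a cohort difference in time to closure would enter the length-of-stay contrast one for one and the PN contrast up to one for one.

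The size in this trial is unknown, and so is the direction. It is zero if the cohorts close equally early. The shifts of 1 to 5 days and the simulated percentages rest on assumed closure differences, distributions and historical cohort size. Enrolment, adherence, fidelity and withdrawal are not affected.

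**What to change.** In Exploratory outcomes and in the section on historical controls:

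- Keep total hospital days and total PN days as defined.
- Add two measures to the historical comparison: days from final closure to discharge, and PN days after final closure.
- Report time from birth to final closure in both cohorts.
- State in advance that a difference in a total will be read as consistent with early feeding only if the closure-anchored contrast shows it too.

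The cost is a few sentences and two more exploratory contrasts. No new data item is needed, because the date of final closure is already required for endpoints 2 and 3 in any cohort where they are compared. The closure-anchored measures have their own limit, which should be stated: they can shift the other way if recovery depends on age since birth, and they do not remove differences in severity linked to staged closure. That is why they belong beside the totals and not in place of them.
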